#### Yijinjing Group

The participants in the Yijinjing exercise group will receive 4 weeks of Yijinjing exercise intervention. The course includes the instruction of a 5-step program, involving details such as the breathing rate, meditation method, extension rotation angle, and how to use your back muscles. Each session consisted of a warm-up for 5 minutes, 20 minutes of Yijinjing exercises, and 5 minutes of calming activities. The specific action characteristics are shown in Figure 2 and Table 2 (Multimedia Appendix 3) [25]. During the first week, the instructor guided the participants throughout the entire process, introducing the details and confusion to ensure that the correct exercise routine was followed. The teacher will provide ongoing support and supervision by videoconferencing. Participants were asked to record the time spent practicing in a punch card booklet, which was to be shown to the tutor. At the end of this trial, the participants were asked to return the booklet to the tutor so that the number of exercises could be counted.

**Figure 2 figure2:**
[figure not shown]
All movements of the 5-step program.

**Table 2 table2:** Details of the operation of the Yijinjing exercise. Specific information can be viewed on the Web [25].

Sequence of actions	Action details
Step 1: Resting the palm over the head	Take a step to the left. Raise your hands before your chest with palms up and fingertips facing. Rotate your wrists and raise your palms above your head. Slightly bend your elbow and look upward toward the dorsum of your palm. Lift your heels and stand on your toes. Hold for 5 s. Then, make fists, rotate your wrists, and slowly lower your fists to waist level. Place your whole feet on the ground. Repeat the entire procedure 3 times.
Step 2: Dragging the tail of a 9-cow ox backward	Begin by stepping sideways to the left with your left foot, while internally rotating both feet and slightly bending your knees and hips into a squatting position. Clench your fists and gradually lift them toward your chest. Extend your arms outward until they form a straight line on each side of your body. Rotate your torso to the left while lowering into a lunge position with your left leg bent and your right leg straight. Externally rotate your left forearm and flex your elbow to create a semicircular shape in front of your chest. Simultaneously, internally rotate your right forearm and extend it behind you. Keep your right elbow naturally extended and slightly backward at approximately 30°. Lastly, relax and repeat the sequence on the right side. This exercise should be performed symmetrically on both sides.
Step 3: Nine demons drawing their swords	Step to the left while crossing your hands over your chest and lifting them upward. Separate your hands above your head. With your left hand placed on your neck and your right hand on your back, tilt your head to the left at a 45° angle and twist your waist. Exhale while tightening your hands. Maintain this position for 5 s. Next, lower your hands to both sides of your body and relax as you exhale. Repeat the exercise on the right side.
Step 4: The green dragon probing the claws	Step your left foot sideways to the left while ensuring your feet are shoulder-width apart. Raise both palms upward to waist level while keeping your gaze forward. Extend your left palm diagonally forward and upward and reach above your head while simultaneously rotating your body to the right. Keep your right palm positioned by your waist on the right side to maintain stability. Internally rotate your left arm while turning your palm downward, and bend your torso from the right side while leaning toward the outer edge of your right foot. As you rotate your body to the left, trace a semicircle with your arm in front of your body. Inhale deeply as you gradually straighten your torso while lifting your hands from the right side and retracting them toward your body.
Step 5: A hungry tiger pouncing on its food	Start by positioning your feet shoulder-width apart. Rotate both feet to the left while turning your body in the same direction. Keep your palms facing upward as you lift both hands together until they reach chest level. Rotate your hands outward and lean your body forward while extending your hands forward with force. Arch your back forcefully and bend the front leg while straightening the back leg. Relax your arms, then turn your hands back into fists and slowly bring them down to the sides of your waist. Repeat this movement.
Step 6: Finishing moves	Open your feet as wide as your shoulders. Inhale and open your hands and raise them slowly above your head. Flip your palms. Exhale and press your hands downward and stop at your abdomen. Drop your hands down. Return to the initial preparation position.

#### About SSE

Through graphic media, videos, and personal dialogue, participants received detailed explanations of biopsychosocial knowledge related to LBP. The educational content will aim to better understand pain, promote healthy work and lifestyle habits, and encourage moderate physical activity. These educational initiatives will continue throughout the intervention. This study will reference the previously validated SSE program used in published research for its effectiveness in treating a specific population with CLBP [26]. The therapist provided verbal cues and instructions for the stretching postures. Participants were instructed to engage in a warm-up for 5 minutes before the session, 20 minutes of SSE exercises, and a cool-down for 5 minutes afterward. Throughout the sustained stretching phase, participants were encouraged to advance each posture at their own pace. The primary goal was to achieve full back extension and maximum ankle dorsiflexion in each posture. Some postures targeted maximal back muscle abduction, while others focused on back muscle adduction. Participants were also advised to reduce the arching of their lower back (maintaining contact with the surface). Proper breathing techniques were emphasized during all postures, with participants instructed to inhale deeply through the nose, expanding the lower ribcage during inhalation. Exhalation involved lowering the chest and allowing the abdomen to expand. The specific action characteristics are shown in Figure 3 (Multimedia Appendix 4).

**Figure 3 figure3:**
[figure not shown]
SSE protocol. SSE: self-stretching exercises.

### Primary Outcome

The ODI is a disability questionnaire specific to the disease that consists of 10 items (scoring between 0 and 100) [27]. It is among the most frequently used in populations with LBP and is a fundamental measure of outcomes suggested for assessing disability related to pain in this group of patients. The validity, reliability, and responsiveness of the ODI have been demonstrated for individuals with LBP [28].

### Secondary Outcome

#### About NRS

The outcome was pain intensity, which was measured on an 11-point NRS (a score of 0 indicates no pain; 10 indicates the worst pain imaginable) 4, 8, and 16 weeks after the intervention [29,30].

#### Measures of Muscle Strength

The maximal voluntary muscle strength of the extensor and flexor muscles will be measured by isokinetic dynamometry at angular velocities of 90 and 120 deg/s (Biodex System 4 Pro, Biodex Medical System) at baseline and during week 4. Subjects were advised to wear comfortable, loose-fitting clothing on the day of testing. Both the thighs and the backs of the subjects were fixed to the testing chair using straps. The axis of the dynamometer was located on the anterior superior iliac spine of the pelvis of the patient. During the formal test, each patient will be required to fold their arms across their chest and be given verbal encouragement in an attempt to achieve a maximum level of effort. Angular velocities of 90 and 120 deg/s will be applied to 2 sets of 5 maximal waist extensions and flexions with a rest interval of 30 seconds between sets [31]. The Biodex isokinetic muscle strength test method is shown in Figure 4.

**Figure 4 figure4:**
[figure not shown]
Biodex isokinetic muscle strength schematic diagram of the test method.

#### About PCS

The PCS will be used for the assessment of catastrophizing thinking associated with chronic pain. It comprises 13 self-report items, and individual perception determines the total score, which ranges from 0 (indicating no catastrophizing) to 52 (indicating extremely severe catastrophizing). The PCS has demonstrated significant clinical acceptance, good construct validity, excellent internal consistency, and test-retest reliability [32,33].

#### About FABQ

The FABQ consists of 16 items, with items 1-5 measuring how fear avoidance beliefs about physical activity affect LBP and items 6-16 measuring how fear avoidance beliefs about work affect LBP, with each item rated on a scale of 0-6 (from “strongly disagree” to “strongly agree”) [34]. The FABQ has demonstrated robust psychometric properties, and its cross-cultural validity has been confirmed [35].

#### About EQ-5D-5L

The 5-level EQ-5D-5L Questionnaire will be used to evaluate health-related quality of life [36]. It encompasses 5 dimensions: mobility, self-care, usual activities, pain or discomfort, and anxiety or depression. Each dimension consists of 5 levels, which correspond to different points. Additionally, the EQ-5D-5L includes a visual analogue scale ranging from 0 (representing the worst imaginable health) to 100 (representing the best imaginable health) [37].

#### Flexibility

The fingertip-to-floor test is a global stretching assessment that was described and validated by Perret et al [38]. The participant stood barefoot on a 20 cm-high platform with their feet together, and the torso was bent forward as much as possible while the knees, arms, and fingers were extended for the test. The vertical distance between the tip of the middle finger and the platform should be measured with a flexible measuring tape, and the measurement is expressed in centimeters. A test was considered positive when the tip of the middle finger did not reach the platform and negative when it passed through the platform. This test has good psychometric properties [39]. The minimum clinically important difference has not been established, but the minimum detectable change for this test was 4.5 cm.

#### Dosage of Pain-Relieving Medication

The participants may continue to take their usual pain relief medication, such as nonsteroidal anti-inflammatory drugs. Changes in dosage should be recorded on the CRF. Dose diaries are notebooks in which participants record their daily dose of pain medication as well as the duration of the dose. The researcher does not recommend any changes in the medical regimen.

### Data Collection and Monitoring

The data collectors, who are blinded to the subgroups and not involved in other aspects of this study, will accurately record all the data collected into the CRF. Upon completion of this trial, the CRF will be handed over to 2 professional data workers who are also blinded to allocation and who are not involved in other parts of this study. The 2 data workers independently extract the data from the CRF into Excel (Microsoft Corp) and verify the accuracy of the data. All electronic data will be stored on a password-protected server, while all paper data will be kept in a locked filing cabinet. Additionally, deidentified data will be stored separately from the files and filing cabinets containing participant details and trial identification numbers. An electronic data capture system will also be used throughout this study to record any traces of data entry or modification. The Department of Information Science and the Clinical Research Centre of Yueyang Hospital, Shanghai University of Traditional Chinese Medicine, will provide the electronic data capture platform and will oversee the entire process of study data collection and management. They will review this study’s data every 6 months to ensure the quality of this study and the reliability of the data.

### Statistical Analysis

In this study, the principle of intentionality analysis will be used to analyze the data. The safety analysis set will be used to analyze the safety of this study. A statistician who is unaware of the group assignments will use SPSS statistical software (version 26.0; IBM Corp) to analyze the data. All effects will be estimated using 95% CIs, and all the statistical tests will be 2-sided. A *P* value less than .05 indicated statistical significance.

Continuous variables are presented as the mean (SD) if they follow a normal distribution; otherwise, they are presented as medians and quartiles. Categorical variables are presented as percentages. Primary outcomes will be assessed using analysis of covariance adjusted for baseline. For other secondary outcomes, *t*-tests or Wilcoxon rank-sum tests will be used.

Repeated outcomes over time will be compared using linear mixed-effects models with the following fixed effects: (1) time points (categorical), (2) intervention group, (3) time-by-group interaction, and (4) baseline measurement as a covariate. Random intercepts for participant ID will be included to account for within-subject correlations. Additional adjustments will be made for prespecified covariates, including age, gender, and study site (if multicenter). Bonferroni correction was used for multiple comparisons across time points.

Missing data will be replaced according to the principle of carry-over of last observations. Missing values for dropout cases will be imputed using either the last observation carried forward method if the dropout rate is below 5% or the multiple imputation method for a dropout rate of 5% or higher. If the attrition rate exceeds 10%, we use per-protocol analysis to ensure the reliability of this study.

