### Outcome

This study will evaluate the Oswestry Disability Index (ODI), Numerical Rating Scale (NRS), Pain Catastrophizing Scale (PCS), Fear Avoidance Beliefs Questionnaire (FABQ), EQ-5D-5L, the Flexibility Test, and the muscle strength test in the fourth week of the experiment. Furthermore, the results of the ODI, NRS, PCS, FABQ, and EQ-5D-5L will be followed up at the 8th and 16th weeks. The schedule of evaluations is outlined in Table 1 (Multimedia Appendix 2).

**Table 1 table1:** Schedule of enrollment, intervention, and outcome measures.

Enrollment	Screening and allocation	Treatment period		Follow-up period	
	Week 0	Week 1-3	Week 4	Week 8	Week 16
Inclusion or exclusion criteria	✓	—^a^	—	—	—
Informed consent form	✓	—	—	—	—
Medical history	✓	—	—	—	—
Physical examination	✓	—	—	—	—
Eligibility for study	✓	—	—	—	—
Baseline characteristics	✓	—	—	—	—
C-spine x-ray	✓	—	—	—	—
Allocation	✓	—	—	—	—
Intervention	—	—	—	—	—
Yijinjing^b^	—	—	—	—	—
SSE^b,c^	—	—	—	—	—
Outcomes	—	—	—	—	—
ODI^d^	✓	—	✓	✓	✓
NRS^e^	✓	—	✓	✓	✓
PCS^f^	✓	—	✓	✓	✓
FABQ^g^	✓	—	✓	✓	✓
EQ-5D-5L	✓	—	✓	✓	✓
Flexibility test	✓	—	✓	—	—
Muscle strength test	✓	—	✓	—	—

^a^Not applicable.

^b^Two times a week from weeks 1-4.

^c^SSE: self-stretching exercises.

^d^ODI: Oswestry Disability Index.

^e^NRS: Numeric Rating Scale.

^f^PCS: Pain Catastrophizing Scale.

^g^FABQ: Fear Avoidance Beliefs Questionnaire.

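### NRS, PCS, FABQ and EQ-5D-5L fall under two stated analysis rules, one unadjusted and one baseline-adjusted, and nothing says which governs

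*Protocol article*

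**What the plan says.** Under Statistical Analysis, the primary outcome is given analysis of covariance adjusted for baseline. The next sentence reads: "For other secondary outcomes, *t*-tests or Wilcoxon rank-sum tests will be used". No covariate is attached to it. The general rule earlier in the section is "A *P* value less than .05 indicated statistical significance", and "all the statistical tests will be 2-sided".

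The following paragraph begins: "Repeated outcomes over time will be compared using linear mixed-effects models with the following fixed effects". The listed effects are time, group, their interaction and, as the last item, "4) baseline measurement as a covariate", with a random intercept per participant. Age and gender are added; the site term falls away because the trial is single-center. The paragraph ends: "Bonferroni correction was used for multiple comparisons across time points". The number of comparisons is not given.

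The abstract lists pain NRS, PCS, FABQ and EQ-5D-5L as secondary outcomes. The Outcome section schedules them at week 4 and adds that "the results of the ODI, NRS, PCS, FABQ, and EQ-5D-5L will be followed up at the 8th and 16th weeks". Flexibility and muscle strength are measured after baseline at week 4 only (Table 1).

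**The concern.** Four scales satisfy both descriptions: they are secondary, and they are repeated. One rule gives an unadjusted two-group test. The other gives a contrast adjusted for baseline, age and gender, from a paragraph that also carries the Bonferroni correction. In context, the word *other* separates these outcomes from the primary one, not from the repeated ones, and the term for repeated outcomes appears only in the next paragraph.

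A reader of the published plan therefore cannot tell whether, say, an unadjusted P of .03 for pain at week 16 was specified in advance as a positive result. This matters because the Discussion expects a pain benefit lasting to the 3-month follow-up, and would take improved emotional distress measures as evidence of benefit in several dimensions. The Introduction's hypothesis names disability and back muscle strength and covers the rest only as other outcomes. No hypothesis in the article names quality of life, so EQ-5D-5L shares the ambiguity but supports no separately named claim.

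**Working it through.** **Which outcomes meet which rule**

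| Outcome | Secondary? | Visits after baseline | t / rank-sum rule | Mixed-model rule |
|---|---|---|---|---|
| NRS, PCS, FABQ, EQ-5D-5L | yes | weeks 4, 8, 16 | applies | applies |
| Flexibility, muscle strength | yes | week 4 | applies | does not apply |

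The plan gives no figure of its own for this point. The only figure taken from it is the arm size: 106 / 2 = 53, and 53 × (1 − 0.20) = 42.4, so about 42 evaluable per arm.

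**Assumptions, not in the documents**
- Three comparisons in the Bonferroni correction.
- A common correlation r of 0.4 to 0.7 between any two visits, including baseline.
- A true effect of 0 or 0.5 SD at every visit after baseline.
- Complete data, with a baseline-adjusted ANCOVA at each visit standing in for the mixed-model contrast.

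**Thresholds**
- Uncorrected: .05, |z| > 1.960.
- Corrected over three visits: .05 / 3 = .0167, |z| > 2.394.

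**Power at one visit, normal approximation**

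Power ≈ Φ(d·√(n/2) / √(1 − r²) − z), with r = 0 for the unadjusted test. For d = 0.5 and n = 42, d·√(n/2) = 0.5 × √21 = 2.291.
- Unadjusted at .05: 2.291 − 1.960 = 0.331, power 63%.
- Adjusted at .0167, r = 0.5: 2.291 / 0.866 − 2.394 = 0.252, power 60%.
- Adjusted at .0167, r = 0.7: 2.291 / 0.714 − 2.394 = 0.814, power 79%.

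Simulation with t distributions gives values 1 to 3 points lower.

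**Simulation, effect 0.5 SD, 42 per arm, only the adjusted contrast corrected**

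| r | t-test at .05, power | Adjusted at .0167, power | Rules disagree at a given visit |
|---|---|---|---|
| 0.4 | 62% | 52% | 16% |
| 0.5 | 62% | 57% | 17% |
| 0.6 | 62% | 66% | 20% |
| 0.7 | 62% | 77% | 24–25% |

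Disagreement runs both ways. At r = 0.4 the t-test alone is positive in 13.2% of trials and the adjusted contrast alone in 2.8%. At r = 0.7 the figures are 5.2% and 19.9%.

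**The same, with both tests at .0167**

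The rules disagree at a given visit in about 15% (r = 0.4) to 36% (r = 0.7) of trials. The threshold gap is gone, and what remains is the effect of adjustment.

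**No true effect: chance of a positive result at one or more visits, per scale**
- Uncorrected t-tests at all three visits: 13.8, 12.6, 12.3 and 10.8% for r = 0.4, 0.5, 0.6 and 0.7.
- Adjusted contrasts at .0167: 5.3, 4.8, 5.0 and 4.4%.
- Either rule counted, t-tests uncorrected: 14.5, 13.7, 14.0 and 13.0%.
- Either rule counted, both corrected: about 7%.

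**The case against.** The strongest reply is that a coherent reading exists. Table 1 splits the secondary outcomes into those measured once after baseline and those measured three times. If the specific rule overrides the general one, t and rank-sum tests cover flexibility and strength, the mixed model covers the four scales, and neither rule is left empty. That may well be what was meant, and an analysis plan not shown here may say so. But the published text does not limit the t-test sentence in this way. Two different tests for the same outcomes is a conflict in what is stated, not a detail left out.

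Four stronger readings are tempting, and the documents do not support them:
- *The plan sets two different thresholds.* This is inferred only from where the Bonferroni sentence stands. Its wording does not exclude t-tests repeated across visits, and the count of three is assumed.
- *The overlap raises false positives to 11–15%.* That requires uncorrected t-tests at all three visits, which no sentence states. Even then, most of the excess comes from the missing correction: counting either rule adds only about 1 to 2 points over the t-tests alone.
- *The adjusted model always has more power.* Against an uncorrected t-test it has less at r = 0.4 to 0.5 and more at r = 0.6 to 0.7.
- *Disagreement depends on using 42 per arm.* The plan is intention-to-treat with imputation, so 53 per arm is also defensible. Disagreement with only the adjusted contrast corrected is then about 14–21%, which is lower but not negligible.

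**Conclusion.** The concern holds as an unresolved overlap between two stated rules for four secondary scales. It does not depend on how the Bonferroni sentence is read: at 0.5 SD and 42 per arm, the rules disagree at a given visit in about 16–25% of trials if only the mixed model is corrected, and in about 15–36% if both are. The false-positive cost is conditional: about 11–14% per scale if the t-tests were run uncorrected at all three visits, against about 7% for either rule if both are corrected. All these figures rest on the assumed correlations, effect and number of comparisons, and on a visit-wise ANCOVA in place of the mixed model.

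This should be put right, but it does not touch the primary conclusion. Flexibility and muscle strength are not affected, because only one of the two rules applies to them.

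**What to change.** In Statistical Analysis, replace the sentence on other secondary outcomes with two statements:
- NRS, PCS, FABQ and EQ-5D-5L are analysed by the baseline-adjusted mixed model already described, with Bonferroni-corrected group contrasts at weeks 4, 8 and 16.
- t or rank-sum tests apply only to secondary outcomes measured once after baseline, that is, flexibility and muscle strength.

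If a rank test is wanted for skewed scores on the repeated scales, label it a sensitivity analysis. There is no need to go further and rule on what such a test may be cited for.

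The cost is a change of wording; no new data or method is needed. The small downside is a stricter per-visit threshold than an uncorrected t-test would have. The article says that analysis had not begun, but it expected publication in January 2025 and appeared in May 2025. The authors should therefore state whether the choice was fixed before the results were seen, and if it was not, report it as a later clarification.

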### Sample Size Calculation

The calculations are based on hypothetical changes in the ODI at week 6. We use the results of a randomized controlled trial to formulate the intended effect. We hypothesize a 3.57-point improvement on the ODI scale in the Yijinjing group compared to the control group [20]. The sample size for each group provided 90% power, and these differences were detected using PASS software (version 15.0.5; NCSS, LLC) at a 2-sided significance level of .05. Considering an expected dropout rate of 20%, a total of 106 patients are required for this study.

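### The repeated-measures model gives baseline one slope for weeks 4, 8 and 16; if the true slope changes across visits, a baseline-by-time term would recover a little precision at almost no cost.

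*Protocol article*

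**What the plan says.** The Statistical Analysis section of the protocol article specifies a linear mixed model for outcomes measured repeatedly. Its fixed effects begin with "1) time points (categorical), (2) intervention group, (3) time-by-group interaction" and end with "4) baseline measurement as a covariate". The correlation within participants is handled as follows: "Random intercepts for participant ID will be included to account for within-subject correlations". No product of baseline and time is listed.

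The visits come from the Outcome section and Table 1. After a week-4 assessment, "the results of the ODI, NRS, PCS, FABQ, and EQ-5D-5L will be followed up at the 8th and 16th weeks". Five scales therefore have three post-baseline visits each.

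Two neighbouring statements limit the reach of the point. For the primary outcome the section names a separate method: "Primary outcomes will be assessed using analysis of covariance adjusted for baseline". For comparisons between visits it says: "Bonferroni correction was used for multiple comparisons across time points".

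**The concern.** The model allows the treatment effect to change from visit to visit but not the relation between the outcome and its baseline value. Week 4 is the end of treatment, and weeks 8 and 16 lie 4 and 12 weeks beyond it. If the regression slope on baseline is steeper at week 4 than at week 16, a single averaged slope adjusts too little at week 4 and too much at week 16. Both departures leave variance in the group contrast that the collected baseline data could have removed.

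A second consequence concerns durability. The Introduction hypothesises short- and long-term benefit, and the Discussion expects effects to last through follow-up. The contrast for this is the difference between the group effects at two visits. With a common slope and complete data, the same baseline correction is subtracted at both visits and cancels, so this contrast is not adjusted for any chance baseline difference between the arms.

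At stake is a modest amount of precision in the visit-specific and between-visit contrasts of ODI, NRS, PCS, FABQ and EQ-5D-5L.

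**Working it through.** **Inputs from the article.** Visits at weeks 4, 8 and 16; 53 per arm; 90% power; two-sided 0.05; 20% dropout; and "We hypothesize a 3.57-point improvement on the ODI scale in the Yijinjing group compared to the control group".

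**Inputs not in the article (assumptions).** The SD of the ODI; the correlations r of baseline with each visit; equal SDs at baseline and all visits, so that slope and correlation coincide; a Bonferroni level of 0.05/3 for three visits.

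**Step 1: the plan's own figure.** The total of 106 cannot be reproduced from stated inputs, because no SD is given. It can be solved backwards. With SD 5.0, n = 2 × (1.960 + 1.282)² × 5.0² / 3.57² = 41.2, so 42 per arm; 42/0.8 = 52.5, so 53 per arm and 106 in total. An SD of about 5.0 to 5.1 is used below only to put the loss on a power scale.

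**Step 2: variance at one visit.** With complete data and a random intercept, the common slope s is the mean of the three visit slopes. In units of the outcome variance:

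- common slope: 1 − 2·s·r + s²
- visit-specific slope: 1 − r²

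For .7/.5/.3, s = .5:

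- week 4: (1 − .70 + .25)/(1 − .49) = .55/.51 = 1.078
- week 8: .75/.75 = 1.000
- week 16: (1 − .30 + .25)/(1 − .09) = .95/.91 = 1.044

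For .6/.5/.4, s = .5:

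- week 4: .65/.64 = 1.016
- week 16: .85/.84 = 1.012

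**Step 3: range, with power.** Power is for 3.57 points, 42 per arm and SD 5.05. For example, at .7/.5/.3, week 16 and level 0.05, the common slope gives 3.57/(5.05 × √.95 × √(2/42)) = 3.32 and power Φ(3.32 − 1.96) = .914.

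| Correlations, weeks 4/8/16 | Variance excess, week 4 | Variance excess, week 16 | Week-16 power at 0.05, common vs by-visit | Same at 0.05/3 |
|---|---|---|---|---|
| .6/.6/.6 | 0 | 0 | .982 vs .982 | .951 vs .951 |
| .6/.5/.4 | 1.6% | 1.2% | .940 vs .942 | .869 vs .873 |
| .7/.6/.5 | 2.0% | 1.3% | .960 vs .963 | .907 vs .911 |
| .6/.45/.3 | 3.5% | 2.5% | .918 vs .925 | .832 vs .842 |
| .7/.5/.3 | 7.8% | 4.4% | .914 vs .925 | .824 vs .842 |

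Week 8 shows no loss in any row, because its slope equals the mean in these linear patterns. Expressed in patients, 7.8% is 53 × (1 − 1/1.078) = 3.8 per arm, and 1.6% is 53 × (1 − 1/1.016) = 0.8 per arm. An extreme fall of .8/.5/.2 would give 25% at week 4 and 9.4% at week 16, with week-16 power of .779 vs .819 at 0.05/3.

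**Step 4: check by simulation** (4,000 trials, N = 106, random-intercept fit, residual correlation .5). For .7/.5/.3 the ratios of standard errors, common slope to by-visit slope, were 1.034/0.999/1.019 without dropout and 1.029/1.001/1.034 with 20% dropout. The formula gives √1.078 = 1.039, 1.000 and √1.044 = 1.022. For .6/.6/.6 the extra terms cost about 0.1-0.3% of the standard error.

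**Step 5: the between-visit contrast.** With a common slope b, the estimate is (D16 − b·d) − (D4 − b·d) = D16 − D4, where D is the raw group difference at a visit and d the baseline difference. No baseline term remains. If the slopes are .7 and .3, a baseline difference of one standard error, √(2/53) = .194 SD, shifts this contrast by (.7 − .3) × .194 = .078 SD. With an SD of about 5, that is about 0.4 ODI points, against a target of 3.57 for the group difference.

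**The case against.** The strongest objection is that nothing in the article shows the slope to change. It gives no correlations and no SDs. A falling correlation would not be enough either, because what matters is the slope, r × SD(visit)/SD(baseline). If r falls from .6 to .5 while the SD rises by 20%, the slope stays at .5 × 1.2 = .6 and nothing is lost. This stands, and it makes the whole point conditional.

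A single baseline covariate beside time, group and their interaction is also a conventional and valid model. Under mild fading the loss is 1-2% of variance, under one patient per arm by the conversion above; a cost of two to four patients would hold only in the steeper cases. This stands too, and it sets the grade.

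A reader might infer that the visit contrasts are biased. They are not: randomisation keeps them essentially unbiased with a common slope, and only precision and the correction for chance imbalance are at issue. A reader might also infer that the primary analysis or the sample size is affected. The article assigns the primary outcome to a baseline-adjusted ANCOVA, which at a single visit estimates its own slope, and the sample size calculation does not refer to the mixed model.

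Finally, a fuller analysis plan, not shown, may contain the interaction. That is possible, but the article enumerates the fixed effects rather than leaving them open, so the list is a fair object of comment.

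**Conclusion.** The point holds as an optional refinement of a stated model. As listed, one baseline slope serves three visits. If the true slopes differ, the group contrasts at weeks 4 and 16 are slightly less precise than the data allow, and the between-visit contrast is unadjusted for baseline when data are complete. Assuming equal SDs and linear fading, the loss runs from nothing up to about 8% of variance at week 4 and 4% at week 16, or about 4% and 2% of the standard error. That is at most about 2 power points for correlations between flat and .7/.5/.3; only a more extreme fall would exceed it.

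The documents do not support the stronger statement that the influence of baseline does fade in this trial, nor that the single-slope model is wrong.

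**What to change.** In the fixed-effects list of the Statistical Analysis section, change item (4) to: *baseline measurement and its interaction with time point*. Each visit then has its own baseline slope, and the between-visit contrasts are adjusted as well.

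The cost is one model term with 2 degrees of freedom, and about 0.1-0.3% of the standard error if the slopes turn out equal. No new data are needed. The Results section reports that analysis had not begun at the time of writing; if that is still so, the term should be fixed before any group comparison is seen.
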